## Abstract

**Background:**

Atopic dermatitis (AD) is one of the most common chronic inflammatory skin diseases, associated with itching, sleep disturbance, and impaired quality of life. Structured patient education can improve disease outcomes, but in-person programs are often unavailable in rural or underserved areas. Digital interventions may help overcome these barriers; however, their efficacy compared with routine care has not been evaluated.

**Objective:**

This study aims to assess whether a digitally delivered, interdisciplinary care concept (ADCompanion) is noninferior to routine, real-world care, as available in well-served areas, in reducing disease severity among patients with AD. Secondary objectives include effects on quality of life, pruritus, psychosocial burden, family well-being, and health care costs.

**Methods:**

This is a prospective, multicenter, 2-arm, 1:1 randomized noninferiority trial. Participants are stratified by age and disease severity. The intervention group receives standard therapy plus access to a digital platform with training modules and optional video consultations on skin care, nutrition, and psychosocial support. The control group receives routine care, optionally including face-to-face group training where available, and a basic app version for symptom tracking. The primary endpoint is physician-assessed disease severity (Scoring Atopic Dermatitis Index [SCORAD]) at 6 months; secondary endpoints include patient-reported outcomes, itch, quality of life, and disease-related costs.

**Results:**

Recruitment of 603 participants across 7 centers in Germany was completed. Data collection was finalized in June 2025. At the time of protocol submission (February 2026), data cleaning had been completed, and the statistical analysis plan was finalized; final results are expected to be published in 2026.

**Conclusions:**

This protocol describes a randomized trial designed to evaluate whether digitally delivered interdisciplinary care is noninferior to routine care for patients with AD. The findings of this study will inform the role of digital patient education as a complementary component within established care structures.

## Introduction

Atopic eczema (atopic dermatitis, AD) is a chronic skin disease with a prevalence of up to 20% in children, depending on the age group [1], and up to 7% of adults [2]. The disease is characterized by chronic inflammation leading to often tormenting itch and chronic skin rashes with potential superinfection. AD often severely impacts the quality of life and sleep of patients and their social environment, particularly when children are affected [3]. Further, an association between early AD and the development of psychiatric disorders such as attention-deficit hyperactivity disorder or autistic spectrum disorders has been described in several studies [4,5]. Among adult patients, an increased prevalence of depression and an average loss of work productivity of 6% have been recently reported in a large registry trial [6]. Despite the availability of effective systemic therapies for moderate-to-severe AD, appropriate topical treatment and daily self-management of flares remain essential components of long-term disease control. The need among patients and caregivers for comprehensive information about the illness and possible forms of treatment and management is often not adequately met during physician consultations, which leads to uncertainty when dealing with important issues such as self-management or stigmatization. As chronic diseases with recurrent exacerbations pose substantial challenges for both patients and health care professionals, specific patient training programs are a key element of several guidelines on AD [7-10]. In Germany, a validated curriculum for group training sessions has been developed, providing multidisciplinary care for individuals and families affected by AD. Its positive impact on the course of disease and quality of life was observed in a pediatric cohort [11] and an adult cohort [12]. A recent scoping review on patient training formats for AD identified 16 studies on different formats such as group-based educational programs, individual consultations with specialized health care providers, pharmacists’ counseling, educational brochures, and online resources [13]. Despite methodological heterogeneity, all concepts resulted in better outcomes compared to no training. Most proposed training programs are designed as in-person group-based formats, taught by an interdisciplinary group of specifically trained health care professionals [11-18]. Although showing positive results, this comprehensive approach requires the availability of qualified staff on site, which can be a limiting factor, particularly in underserved regions. Although during and after the SARS-CoV-2 pandemic, remote care delivery increased exponentially and AD training programs, among others, were delivered online [19], comparative evidence between different care formats remains scarce.

Despite guideline recommendations and established training concepts, long-term disease control in AD frequently remains suboptimal. This is partly driven by challenges in day-to-day self-management, including treatment adherence, uncertainty about trigger management and skincare routines, corticosteroid concerns, and limited opportunities for reinforced counseling in routine visits [20,21]. Consequently, contemporary national and international guidelines emphasize structured patient and caregiver education as a core component of AD management [7,8,10]; however, access to multiprofessional educational programs remains heterogeneous and often limited by local availability, staffing resources, and organizational barriers [22,23].

Digital health interventions may help address these access limitations by delivering evidence-based education and counseling independent of geographical location [24]. Over the past few years, online behavioral and self-management interventions for eczema have shown modest improvements in patient-reported outcomes; however, many digital interventions primarily rely on self-assessed disease severity, while comparative data using clinician-assessed outcomes remain limited [22,23,25]. Beyond patient-level outcomes, unmet needs also affect caregivers and health care professionals involved in AD management, particularly in the context of limited consultation time and fragmented care structures. Families frequently report difficulties in coordinating care, navigating treatment recommendations, and managing disease-related psychosocial stress in everyday life. From a health care provider's perspective, limited consultation time, high demand, and fragmented care structures constrain the ability to deliver repeated, individualized education and follow-up support. Digital care concepts that combine standardized educational content with flexible, needs-based counseling may therefore help reduce structural barriers while supporting continuity of care across sectors and professional groups [10,23,26].

Building on validated multiprofessional educational curricula [11,12], and combining asynchronous education with symptom and trigger tracking as well as optional synchronous video consultations, *ADCompanion* was developed as a comprehensive interdisciplinary digital care concept for patients with AD across age groups. Against this background, this study evaluates whether this digitally delivered intervention achieves noninferior clinical outcomes compared with routine care in well-served regions.

This paper describes the study protocol of a prospective, multicenter, 1:1 randomized 2-arm intervention study with a noninferiority design to test whether the digitally delivered concept of care is equally effective in improving eczema severity (primary objective), pruritus, quality of life, family well-being, and health care–related costs (secondary objectives).

This paper reports the study protocol of the ADCompanion trial and is published after completion of recruitment and data analysis (Registered Report stage DERR1) in accordance with JMIR Protocols guidelines.

## Methods

### Study Aims

ADCompanion aims to evaluate a remote care concept for AD to positively influence the course of disease through (1) digitization of selected and validated patient training content, (2) standardized symptom and trigger recording, as well as optional individual data-supported video consultations in the areas of (3) nutrition, (4) skin care, and (5) psychosocial support. Via this digitally delivered care concept, the authors also aim to improve the quality of life and health literacy of patients/caregivers to ensure long-term participation in the social and professional/school context.

### Study Design

ADCompanion is a prospective, multicenter, 1:1 randomized 2-arm intervention study with a noninferiority design. Patient enrollment is stratified in 3 age groups: infants, toddlers, and preschool children (age 3 months to 6 years); school children and adolescents (age 7‐17 years); and adults (age 18‐65 years). The need for this stratification results from known differences in care between age groups and a high spontaneous remission rate in preschool age.

The study groups differ as follows: The control group receives standard therapy (optionally including access to face-to-face training in small groups where possible, in line with routine care) and access to a limited version of the study app containing standardized symptom and trigger recording only. Routine care in this trial reflects routine real-world care as delivered across participating centers and does not mandate participation in structured face-to-face education programs. The intervention group receives standard medical therapy without access to face-to-face group training, but with full use of the app, including online training content and optional individual counseling via video in the areas of care, nutrition, and psychosocial support. Participants can freely decide which counseling sessions they want to book. Per specialist area, a maximum of 3 sessions can be booked during the first monitoring period (6 months). For an overview on the study visits and timeline, please see Figure 1. Due to the nature of the intervention, blinding of participants or investigators was not feasible and therefore not applied.

**Figure 1. F1:**
[figure not shown]
Overview of the study timeline and visits.

Patients were recruited in the outpatient departments of 7 German hospitals—Berlin (pediatric and dermatology departments), Bielefeld (pediatric department), Dresden (pediatric and dermatology departments), Erlangen (dermatology department), Hannover (dermatology department), Munich (dermatology department), and Nürnberg (pediatric department). The study has been approved by all local ethics committees and is registered at the German Clinical Trials Register (ID: DRKS00030902).

This study received public funding from the Innovation Fund of the Federal Joint Committee of Germany, which serves as a central policy instrument to advance health care delivery in Germany.

### Participants and Recruitment

Patients with a physician-confirmed diagnosis of AD were recruited consecutively between May 2023 and May 2024 from the outpatient departments of 7 university and community hospitals across Germany (Berlin, Bielefeld, Dresden, Erlangen, Hannover, Munich, and Nuremberg). Potential participants were identified during routine visits and informed about the study by trained study personnel. Additionally, flyers and posters that informed about the study were placed in doctors’ waiting rooms, hospital hallways, and preschools. The statutory health insurance and project partner “Techniker Krankenkasse” further sent out 73,000 informative leaflets to clients with a diagnosis of atopic eczema. After providing written informed consent (or parental consent for minors), participants were screened for eligibility criteria (Textbox 1). Ongoing systemic therapies were no exclusion criterion, as long as a Scoring Atopic Dermatitis Index (SCORAD) of ≥20 points was reached. To promote retention, a small compensation fee of €30 (US $34.72) for participants of the intervention and €60 (US $68.73) for patients in the control group was given after completion of the final study visit.

Textbox 1.Criteria for inclusion and noninclusion.
**Inclusion criteria**
Age 3 months to 17 years (children/adolescents) or 18-65 years (adults)A medically confirmed diagnosis of atopic dermatitis (AD) that has existed for at least 3 monthsModerate to severe AD (Scoring Atopic Dermatitis Index [SCORAD] of ≥20 points)Stable treatment regimen for the last 3 months (eg, no new use of systemic therapies planned)Possession of an internet-enabled smartphone (for children under 14 years of age, possession of the smartphone by the parents is decisive)Confident command of the German language (for young children, the parents’ command of the German language is decisive)Enrollment in German statutory health insurance
**Exclusion criteria**
Participation in a rehabilitation or training program for AD in the last 2 yearsParticipation in individual counseling pertaining to AD in the areas of care, nutrition, and/or psychosocial support in the last 12 monthsPlanned, significant change in treatment regimen (eg, first-time use of biologics) in the next 6 monthsOther serious illnesses that may have an impact on the skin condition (eg, autoimmune diseases)

### Randomization

Randomization was performed according to the following strata in a 1:1 ratio in the intervention and control groups: (1) study centers, (2) age (children aged 3 months to 6 years, children aged 7‐17 years, and adults aged 18‐65 years), and (3) disease severity (patients with a SCORAD of 20‐50 points were categorized as mildly/moderately and patients with a SCORAD of >50 points as severely affected).

Due to the high number of strata, unbalanced results may occur in a simple randomization with regard to the stratification variables between the intervention group and the control group. To ensure balanced treatment assignment across multiple prognostic factors, participants were assigned to either the intervention or control group (1:1 ratio) using a deterministic variance minimization algorithm [27]. The stratification factors included study center, age (3 months to 6 years, 7‐17 years, and 18‐65 years), and baseline SCORAD (cutoff of 50 points). While the algorithm did not use a random element (eg, a biased coin), allocation concealment was strictly maintained as the automated assignment was generated by a web platform only after the successful completion of the baseline assessment and recruitment. Given the complexity of the balancing across numerous strata and the centralized, software-based nature of the allocation, the treatment path was not accessible to the investigating clinicians, thereby minimizing the risk of selection bias. Randomization took place after informed consent, after download of the study app, and after the baseline survey via computer software, with no influence of investigators. Due to the app-based onboarding process and immediate assignment within the digital system, full blinding was not feasible; however, treatment allocation could not be influenced by study personnel.

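### Hiding the software does not make deterministic minimisation by centre unpredictable in an open-label trial, so the claim that selection bias risk was minimised is not supported

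*Protocol article*

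**What the plan says.** All references are to the protocol article.

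- **Method (Randomization).** Patients were assigned 1:1 "using a deterministic variance minimization algorithm". Centre, three age bands and baseline SCORAD (cutoff 50) were the balancing factors: "The stratification factors included study center, age (3 months to 6 years" and so on.
- **No random element (Randomization).** "While the algorithm did not use a random element (eg, a biased coin), allocation concealment was strictly maintained". The reason given is that a web platform produced the arm only once baseline and recruitment were complete.
- **Conclusion drawn (Randomization).** From the complexity of balancing and the central software, the article concludes that "the treatment path was not accessible to the investigating clinicians, thereby minimizing the risk of selection bias".
- **Timing (Randomization).** "Randomization took place after informed consent, after download of the study app, and after the baseline survey via computer software".
- **Blinding (Study Design).** "blinding of participants or investigators was not feasible and therefore not applied".
- **Recruitment and screening.** Participants and Recruitment describes consecutive enrolment. Results reports that screening failures were not logged systematically and that a SCORAD under 20 was often the reason for noninclusion.
- **Limitations (Discussion).** Predictability of allocation is not among them.

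**The concern.** Two properties are being treated as one. Concealing the generated arm until a patient is enrolled stops staff from looking it up. It does not stop them from inferring it from what has already happened. With no random element, and apart from ties, the next arm is a fixed function of earlier assignments and the new patient's factor levels. Because centre is one of the factors, the centre's own history pushes the next patient towards the arm that is behind. In an open trial, staff can learn that history.

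Assignment after consent and baseline does not remove the problem. A guess can influence whom to approach, when to enrol, and how SCORAD is rated near the entry threshold of 20 or the cutoff of 50, all before the software runs. If that happened, the arms could differ in prognosis in ways the primary model would not fully correct. The model adjusts for baseline SCORAD, age and centre, but not for unmeasured prognosis. The comparison is judged against a margin of 4 SCORAD points, and a bias could run in either direction.

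**Working it through.** The article gives no figure for predictability, so there is none to reproduce. The check simulates the design as described.

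**Inputs from the article**
- 603 patients and 7 centres: "Recruitment of 603 participants across 7 centers in Germany was completed".
- Age mix 252 / 146 / 205 (Results).
- Factors: centre (7 levels), age (3), SCORAD category (2). The algorithm was modelled as balancing 7 + 3 + 2 = 12 marginal totals, not 7 × 3 × 2 = 42 separate cells.

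**Assumptions, because the article does not state them**
- Share with SCORAD above 50: 10%. A normal approximation to baseline mean 34.72 and SD 11.64 gives z = (50 − 34.72)/11.64 = 1.31, an upper tail of about 9.5%. Values of 5–20% were tried.
- Ties broken at random, or by a fixed rule.
- Centres of equal or unequal size; 7 hospitals or 9 departments; mixed or mainly paediatric/adult sites.
- Imbalance measured by summed squares, or by range.

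**Rule simulated.** For a new patient, add the current arm differences over the patient's centre, age band and SCORAD category, and assign the arm that reduces the imbalance. Staff guess the arm with fewer patients at their own centre, and guess at random when the tally is even.

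**Full own-centre tally (7 equal centres, random ties)**

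| Centre tally before enrolment | Share of enrolments | Guess correct |
|---|---|---|
| Even | 38.3% | 50.2% |
| Differs by 1 | 48.9% | 76.8% |
| Differs by 2 or more | 12.7% | 93.9% |

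- Overall: 0.383 × 0.502 + 0.489 × 0.768 + 0.127 × 0.939 = 0.687, about 69%.
- Uneven tally only: (0.489 × 0.768 + 0.127 × 0.939)/(0.489 + 0.127) = 0.495/0.616 = 0.80.
- Across all the assumptions above, the overall rate stays at about 68–71%.
- With centre removed as a factor, the same guess is right 50% of the time. The predictability at site level therefore comes from balancing on centre.

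**Less than full knowledge**
- Own department only. Berlin and Dresden each list a paediatric and a dermatology department. With nine equally recruiting departments and balancing by hospital, the guess is right in about 62% overall and about 53% at those two hospitals.
- Full centre tally except the most recent allocation: about 56%.

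**A conventional comparator.** For permuted blocks of size 2m within centre, the same guessing rule has an expected number of correct guesses per block of m + [2^(2m)/C(2m, m) − 1]/2.
- Block of 4 (m = 2): 2 + (16/6 − 1)/2 = 2.83; 2.83/4 = 71%.
- Block of 6 (m = 3): 3 + (64/20 − 1)/2 = 4.10; 4.10/6 = 68%.

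**The case against.** The strongest reply has four parts.

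1. **The 69% needs a complete, current tally.** Nothing in the article says that staff kept one. Assignment was automated within the app, and lack of blinding does not show that recruiters followed every allocation in order. This stands, and it is why the lower range of 56–62% belongs beside the 69%.
2. **The method is no worse than common practice.** Blocks of 4 or 6 within centre give 71% or 68%. This also stands. The fault is not that an unacceptable method was used but that a property is claimed which the method lacks.
3. **The article is open about the method.** It already calls the algorithm deterministic and volunteers that there was no biased coin. That is correct, so no renaming is needed. What remains is the inference drawn immediately afterwards.
4. **Nothing shows that selection took place.** Recruitment was consecutive, the baseline rater did not yet know that patient's arm, and mean baseline SCORAD was 34.88 against 34.57. This is mildly reassuring. However, SCORAD category was itself balanced by the algorithm, so similar means say little about other prognostic factors. Without a systematic screening record, selective enrolment cannot be audited from a screening log.

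A reader might go further and infer that sites could foresee almost every assignment. In the simulation with random ties, about 90% of assignments can be guessed, but only by someone holding trial-wide counts by centre, age and severity. The article nowhere gives sites those counts, so this is not a site-level risk. A reader might also infer that the trial was biased; the article contains no evidence of that.

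**Conclusion.** The point holds as an unsupported claim about a core safeguard. The stated grounds (complex balancing, central software, assignment after baseline) protect the generated arm from being seen. They do not make it unpredictable, and so do not justify saying that selection bias risk was minimised.

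The size is moderate: about 69% correct guesses with the full own-centre tally, about 80% when that tally is uneven, and about 56–62% with department-only or delayed knowledge, against 50% by chance. These figures rest on assumed centre sizes, severity share, tie rule and imbalance measure. The full-tally result moved little over the ranges tried. What staff actually knew matters more, and the article does not report it.

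The finding concerns an opportunity for bias, not its occurrence. It does not affect the sample size or the endpoint.

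**What to change.** 1. **Wording.** In Randomization, replace "thereby minimizing the risk of selection bias" with a statement that the generated arm was hidden until after baseline assessment, but that allocation was partly predictable from earlier allocations at the same centre. Add this to the limitations in the Discussion.
2. **Check from the existing log.** For each patient in order of entry, derive the predicted arm from the centre's prior counts (the arm behind, or neither if even). Report a Berger-Exner check and a sensitivity analysis that adds this predictor to the primary model. Use the centre-count predictor, not the full assignment probability: with all tallies known, about 75–80% of assignments are fixed before any tie, so that probability would nearly duplicate treatment arm.
3. **Labelling.** The Abstract says that cleaning is done and the SAP finalised, while the Introduction and Results say that data analysis is complete. If analysis has begun, call the check post hoc. A null result would be reassuring but would not exclude selection, since the predictor reflects only one way of guessing.

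Recruitment is closed, so the allocation method itself cannot be changed. The cost is a few sentences, a short analysis of data already held, and a less favourable statement about allocation.
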